## Abstract

**Background:**

Modifying the built environment by improving parks is potentially a sustainable way to increase population level physical activity. Despite considerable investment in parks and park renovations, few natural experiments on the impact of improving amenities on park use and park-based physical activity have been conducted. REVAMP is a natural experiment that aims to examine whether park improvement increases overall park usage, park-based physical activity and active travel to and from the park in the intervention compared with the control park over a two-year period; and to identify which specific aspects of the park refurbishment attracts park visitors and encourages park users to be more active. This paper describes the methods of the REVAMP study.

**Methods:**

The intervention park is a large regional park (329 hectares) located in a low socio-economic status (SES) area in the north-eastern suburbs of Melbourne, Australia. The control park is a regional park (120 hectares) located in a high SES area in the eastern suburbs of Melbourne. Multiple methodologies to evaluate the impact of the park renovation are being employed including: cross-sectional surveys of local residents living near the two parks, direct observations of park users, intercept surveys with park users, and electronic monitoring of path usage and car traffic within the parks. Baseline measures were conducted in April-May 2013 (T1), and an innovative play space suitable for children of all ages and abilities was installed at the intervention park between September 2013 and February 2014. Follow-up measures will be repeated in April-May 2014 (T2) and April-May 2015 (T3). All methodologies will be completed at both the intervention and control parks at all three time-points, with the exception of the cross-sectional survey of local residents which will only be conducted at T1 and T3.

**Conclusion:**

This research will inform future park developments, and will contribute to creating an evidence base of the impact of park refurbishment, and the development of natural experiment methodology.

**Trial Registration:**

Current controlled trial ISRCTN50745547, registration date 11.1.2014.

## Background

Modifying parks by improving access and optimizing their design to encourage activity is potentially a sustainable way to increase population-level physical activity. Parks are located in most neighbourhoods, they are generally free to access, offer a variety of opportunities for physical activity and can serve diverse populations [1]. Research shows that park availability, proximity and access are associated with higher overall levels of physical activity [2] and spending time in parks can be restorative and beneficial to mental health [3]. There is also evidence that physical activity undertaken in parks or green-spaces may have greater psychological and physiological benefits than physical activity in other settings [4,5]. Given that physical inactivity is a major contributor to the burden of chronic disease, including cardiovascular disease, diabetes, and overweight and obesity [6,7], understanding how to attract residents to parks and encourage park users to be physically active is an important public health goal.

Parks may encourage physical activity in two ways: as an important destination to which people walk or cycle (i.e. active transport) [8] and as a destination for physical activity whereby the presence of a high quality park may encourage increased physical activity within the park [9]. Both of these ‘opportunities’ for physical activity may make substantial contributions to overall physical activity levels and therefore benefit public health. Just having a park located close to home; however, may be necessary but insufficient for promoting physical activity. Observational studies of park use in the USA have shown that more than half of park users engaged in sedentary behaviour (primarily sitting) during their park visit [10,11]. A number of studies have found park quality and specific park features to be a major factor associated with achieving recommended levels of activity [9,12-14]. However, an Australian study found that a wider range of activities, including sedentary behaviours such as picnics and sitting, took place in more attractive parks [12]. While this may benefit mental health, without active transportation to the park, it will have little impact on physical activity and thus risk of chronic disease. Hence, simply making parks attractive for users may not be enough to increase community-wide physical activity levels. Understanding specific park features that attract users and encourage park-based physical activity is therefore important.

Improving parks may be particularly advantageous for increasing physical activity levels among disadvantaged populations where residents do less recreational physical activity [15] and are at an increased risk of inactivity and associated poor health outcomes [16]. For example, in the UK the increased risk of all-cause and circulatory disease mortality related to socio-economic disadvantage has been shown to be lower in those living in the ‘greenest’ areas (i.e., areas with more parks) compared with those who have less exposure to parks [17]. Although previous research in Melbourne Australia, showed no differences in park access according to area-level socioeconomic disadvantage (adjusted for population density) [18], parks in low socio-economic status (SES) areas have fewer amenities and features likely to promote physical activity among children than do parks in higher SES areas [19]. The importance of conducting natural experiments on open spaces for disadvantaged populations has recently been recognised [20].

Natural experiments enable researchers, in the absence of randomised controlled trials, to evaluate the effectiveness of ‘real world’ policy interventions that have not been manipulated by the researcher [21]. Natural experiments have been identified as a priority for investigating causal associations between the built environment and physical activity [22]; both in terms of increasing the evidence-base regarding environmental determinants of physical activity, and for identifying effective environmental interventions and policies to promote physical activity [23]. Due to the substantial financial costs and logistical challenges of conducting research involving major modification of the built environment, there is little research in this area. Rather, these studies need to be opportunistic. A few natural experiments examining physical activity have monitored the development of neighbourhood greenway/trails [24], sporting playfields [25], walking/cycling trails [26,27], and the implementation of new residential development codes [28], with results showing some increases in overall path use [24] and visits to the sporting playfields [25]. However, limited research has focused specifically on parks.

In the USA, a study examining the impact of improvements to five parks showed a decline in park use in both the intervention and control parks although this may have been attributable to simultaneous cuts to within-park programming [29]. Another study in USA that evaluated the impact of installing outdoor exercise equipment in 12 parks showed a non-significant increase in park usage in the intervention compared with control parks [30]. However, the follow-up observations were conducted at different times of the year and the period between measurements were not consistent between parks. In Australia, a study examining impact of playground renovation on usage and physical activity found no detectable difference in use or in children engaged in moderate- to vigorous-intensity physical activity at follow-up [31]. In contrast, another natural experiment study in Australia, which examined the impact of improvements at a small neighbourhood park on park usage and park-based physical activity, showed significant increases in park use (T1 = 235, T3 = 985) and people engaged in park-based vigorous activity (T1 = 38, T3 = 257) following park refurbishment [32]. That study provided evidence that park improvement has the potential to dramatically increase park usage; however, it focused only on improvements involving the installation of a small playground, walking track, and off-leash dog walking area in one park. Further evidence of the impact of park refurbishment in more diverse parks, in terms of size and features, and in neighbourhoods with residents of varying socio-demographic profiles is needed.

In summary, if neighbourhood parks are to attract more users and facilitate increased physical activity, research is needed to better understand park use, the activities park users engage in whilst at the park, and what improvements to park facilities result in increased park use and physical activity levels. Despite the considerable public funds invested in park renovations, little research evidence exists examining whether improving amenities in parks actually increases park use or park-based physical activity. This paper presents an overview of the aims, methodology and design of the REVAMP study, which seeks to address this gap.

### The REVAMP study

#### The intervention

REVAMP (Recording and EValuating Activity in a Modified Park) is a natural experiment examining the impact of the refurbishment of a large regional park (Brimbank Park) located in an area of low SES of Melbourne, Victoria, Australia. Specifically, the three main research objectives are to:

1. Examine whether park improvement increases overall park usage in the intervention park compared with the control park;

2. Examine whether park improvement increases the proportion of local residents engaging in park-based physical activity and active travel to and from the park in the intervention compared with the control park; and

3. Identify the specific aspects of the park refurbishment that attract visitors to the park and encourage park users to be more active.

The refurbishment of Brimbank Park commenced in September 2013 and was completed in February 2014. It involved the installation of an innovative play space suitable for children of all ages and abilities. This circumstance provided a rare opportunity to undertake a natural experiment, to observe changes that occur in a population before and after the park environment has been altered. Whilst the redevelopment will focus on the installation of a play space for children, it is important to assess the broader impact of the refurbishment on parents, families, adults and older adults.

As well as being accessible by road, Brimbank Park (329 hectares) is accessible via a shared path for walking and cycling that stretches 28 km north-west from Melbourne’s central business district (CBD). Within the park is a further 4.3 km shared path circuit. The City of Brimbank has a total population of almost 190,000 residents. The demographic profile of residents is diverse, with a high proportion of children aged 0–9 years (12.7%), a growing indigenous population (currently 0.4%), and a high proportion of residents born overseas (49.6%) [33].

#### The control park

Westerfolds Park (120 hectares) is located 22 km east of Melbourne’s CBD. This park was selected to match as closely as possible to the intervention park prior to refurbishment using the following criteria: 1) park features (i.e. mainly open spaces and picnic areas); 2) park size; 3) accessibility via a shared walking/cycling path; and 4) availability of a sealed walking/cycling path within the park. The control park is located in a more socio-economically advantaged area of Melbourne; however, it was not possible to find a matching large park in a disadvantaged area with similar features to the intervention park. Importantly, there are no planned improvements or changes to the control park during the study period.

## Methods

Baseline data collection occurred in April-May 2013 (T1, prior to the refurbishment commencing), in both the intervention and control parks. Follow-up will be conducted at both parks at one-year intervals, Time 2 (T2, 2014) and Time 3 (T3, 2015) with each data collection to take place at the same time of the year to account for seasonal effects. The inclusion of two measures post-refurbishment allows time for residents to become aware of the new facilities [32]. To address the study aims, multiple methodologies will be employed including: cross-sectional surveys of local residents living nearby the two parks, direct observations of park users, intercept surveys with park users, and electronic monitoring of path usage within the parks and of vehicles entering and exiting on-site car parks.

### Neighbourhood survey

Cross-sectional surveys of adults living within 5 km of the two parks will be employed at T1 and T3 to determine population changes in park use. Surveys will not be distributed at T2 as there is insufficient time between completion of the park refurbishment and T2 data collection to obtain data on usual park visitation. A longitudinal design is typically used for measuring within-person increases in behaviour; however, a repeated cross-sectional survey was considered the most appropriate for determining population-level increases. As the intervention is a play-space it is important to recruit families with children aged between 2–15 years. To obtain participants with these demographic characteristics, recruitment was via two methods: 1) families with children attending pre-schools, primary and secondary schools located within 3 km of each park; and 2) a postal survey from the local City Council to households located within 5 km of each park.

#### Recruitment via schools

For baseline measures, pre-schools, primary (elementary) and secondary government and Catholic schools located within a 3 km buffer surrounding the two parks were emailed and contacted by telephone and invited to participate. Recruitment of schools continued until six pre-schools, ten primary schools and two secondary schools were recruited. This number of schools resulted in approximately 5,000 eligible families (2,500 from each area) with children aged 2–15 years attending schools in both the Brimbank and Westerfolds areas. Once the schools consented to participate it was arranged for a survey to be sent home to: all families at each preschool with a child aged 2 years or older; every family at each primary school; and all families at each secondary school with an adolescent in school years 7–9. The survey envelope included a plain language statement, a consent form, a survey, and a reply-paid envelope for survey return.

Information on the study was placed in school newsletters in the week prior to surveys being distributed. In order to encourage survey return, reminder postcards were sent home to each family two weeks and six weeks after the surveys had been distributed and where possible a further reminder was placed in school newsletters.

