#### Sample size calculations

Sample size calculations for the neighbourhood survey were based on ordered logistic regression analyses from a previous pilot natural experiment study in parks [32] by comparing responses for use of control and intervention parks post-refurbishment. This analysis yielded an estimated Odds Ratio (OR) across seven categories of frequency of park use (i.e. from ‘most days’ to ‘have not visited in the past 6 months’) of 4.74 [2.71, 8.33]. The proportional odds assumption was violated (p = .026), meaning that the OR at each category was not similar enough to summarise into one OR, therefore, generalised ordered logistic regression calculating six OR’s across seven categories was performed. Using a conservative approach, the smallest individual OR (1.41) was used in the following calculations. With alpha = 0.05 (two-tailed), beta = 0.20, this gives a required sample size of 444 at each time point [43] for both adults and children.

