#### Baseline response rate

From the 9649 surveys distributed, 1488 surveys were returned completed, with 866 surveys including data on children. A total of 4637 surveys were distributed via pre-schools and schools with 713 returned (15.4% response rate). A total of 4984 surveys were distributed via the two Councils with 772 returned (15.5% response rate) and 22.5% including responses about children. Twenty-eight Vietnamese surveys were requested; however, only three (11% response rate) were returned completed.

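### The survey sample size of 444 carries no stated allowance for school clustering, which overstates its 80% power, mainly for children

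*Protocol article*

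**What the plan says.** All references are to the Protocol article.

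- **Recruitment via schools.** "Recruitment of schools continued until six pre-schools, ten primary schools and two secondary schools were recruited". By the article's count these sites held about 5,000 families who could be surveyed, half of them in each area. Surveys went home to all eligible families at each site, so the school is the sampling unit of this stream.
- **Recruitment via postal survey.** The second stream is a random sample of 5,000 residents, 2,500 per park area. It is not clustered by school.
- **Baseline response rate.** "A total of 4637 surveys were distributed via pre-schools and schools with 713 returned". The postal stream returned 772, of which 22.5% carried child data. In total there were 1,488 returns, 866 of them with child data.
- **Sample size calculations.** The effect size comes from an earlier pilot natural experiment "by comparing responses for use of control and intervention parks post-refurbishment". Because proportional odds failed there, "generalised ordered logistic regression calculating six OR’s across seven categories was performed", and "the smallest individual OR (1.41) was used in the following calculations". The result is: "With alpha = 0.05 (two-tailed), beta = 0.20, this gives a required sample size of 444 at each time point". The same figure serves adults and children. No ICC, design effect or other clustering allowance is mentioned.

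The article does not set out how the survey data will be analysed.

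**The concern.** Families at one school plausibly share locality, distance to the park and the age band of their children, so their park-use answers are unlikely to be independent. In a between-park comparison, where schools are nested within areas, such correlation inflates the variance of the school stream. A calculation that counts respondents as independent then promises more power than it delivers.

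The two populations are also not equally exposed: roughly half of the adult data is school-recruited, against four fifths of the child data. One figure for both hides this. At stake is whether the child comparison, which matters because the intervention is a play space, has the power that the article claims.

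**Working it through.** **1. The plan's own figure.** Inputs: OR 1.41, two-sided alpha 0.05, power 80%, seven ordered categories. The category proportions are not given, so 444 cannot be reproduced exactly. I used the Whitehead formula for ordinal data with equal groups; this is my choice, as the article's cited source is not at hand:

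N(total) = 12(1.96 + 0.8416)² / [(ln 1.41)² × (1 − Σp³)], with (1.96 + 0.8416)² = 7.849 and ln 1.41 = 0.3436.

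- Seven equal categories (Σp³ = 0.0204): N = 814, or 407 per group.
- 444 per group needs Σp³ of about 0.10, for example one category holding about 46%. That is plausible.
- 444 in total needs 1 − Σp³ = 1.80, which is impossible under this formula. With 444 in total, power is about 54–55%.

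So 444 looks like a per-park number, although the text reads as a total per time point. Neither reading needs or contains a design effect. Below I accept the stated 80% at face value and ask only what clustering does to it.

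**2. Share from schools at baseline.**
- Clusters: 6 + 10 + 2 = 18, both areas together.
- Adults: 713/1,488 = 47.9%. The other 775 are 772 postal plus 3 Vietnamese-language returns (713 + 772 + 3 = 1,488).
- Children: 0.225 × 772 ≈ 174 postal, so 866 − 174 ≈ 692 via schools (79.9%).

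**3. Power at 444 with the baseline mix.** With school share s and m = 444s/18 respondents per school, the overall design effect is D = s[1 + (m − 1)ICC] + (1 − s). Required N = 444D, and power = Φ(2.8016/√D − 1.96). For adults m = 11.8 and for children m = 19.7. The ICC values are assumptions.

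| ICC | Adults: D | N | Power | Children: D | N | Power |
|---|---|---|---|---|---|---|
| 0.01 | 1.05 | 468 | 78% | 1.15 | 511 | 74% |
| 0.02 | 1.10 | 491 | 76% | 1.30 | 577 | 69% |
| 0.05 | 1.26 | 560 | 70% | 1.75 | 776 | 56% |

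If 444 is per park (888 per time point), clusters are larger. Power becomes 76% / 72% / 62% for adults and 69% / 60% / 42% for children.

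**4. What the achieved baseline sample is worth.** In an unweighted analysis, effective n = (total)² / (n_school × DE + n_other), where DE = 1 + (m − 1)ICC. Here m = 713/18 = 39.6 for adults and 692/18 = 38.4 for children. Example, children at ICC 0.02: DE = 1.75, and 866²/(692 × 1.75 + 174) ≈ 542.

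| ICC | Adults (1,488) | Children (866) |
|---|---|---|
| 0.01 | 1,256 | 667 |
| 0.02 | 1,086 | 542 |
| 0.05 | 773 | 347 |

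**5. Break-even ICC.** Against 444 in total: adults 0.127, children 0.032. Against 888: adults 0.037; children are already short without clustering, since 866 < 888.

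**6. If school were ignored in the analysis.** The real error rate of a nominal 5% unadjusted park comparison would be 2[1 − Φ(1.96/√D)], with D taken from step 4. For children D = 1.30 / 1.60 / 2.50, giving about 9% / 12% / 21%. For adults the rate is about 7% / 9% / 16%.

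These figures describe a comparison of parks at one wave, or a change between waves that use different schools. They assume equal school sizes; unequal sizes would raise the design effect.

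**The case against.** Four points can fairly be made against this.

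*The analysis may already handle schools.* A reader might infer that the survey's intervals will be too narrow. The article does not support that. It sets out no survey analysis; its ordered logistic model is the pilot's, used to obtain an odds ratio; and an analysis plan that is not shown may well include school. The error rates in step 6 are therefore conditional. A later plan cannot, however, change the basis on which 444 was published.

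*Nothing says that the schools will change at T3.* This is true. School recruitment is described for baseline only, and silence about T3 is not a plan to replace schools. A claim that swapped schools will distort the T1–T3 change would go beyond the text. Nor would reuse restore all precision: it cancels stable school effects, not school-by-time variation.

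*The practical loss may be small.* For adults this stands if 444 is a total, because the 772 postal returns alone exceed it. For children, 444 is still met at ICC 0.01 and 0.02. If the two streams were weighted by their information (effective n = 174 + 692/DE), the child break-even would rise from about 0.03 to about 0.04. Adjustment for covariates could also lower the residual ICC.

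*The effect size was conservative.* The smallest category-specific odds ratio, 1.41, was used against a summary of 4.74. That gives margin if the true effect is larger, but the 80% is stated for 1.41 and should be correct there.

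**Conclusion.** The point holds in a limited form. The stated 80% power at 444 makes no visible allowance for school clustering and is too high for any positive ICC. The loss is modest for adults (to 70–78%) and material for children (to 56–74%) over an assumed ICC of 0.01 to 0.05. Baseline child returns fall below 444 in effective size only above an ICC of about 0.03; adult returns do so only above about 0.13. If 444 is per park, the adult limit is about 0.037 and the child sample is slightly short before any clustering, which makes that ambiguity worth settling at the same time.

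The size rests on an ICC that the article does not give, on equal school sizes, and on T3 resembling the baseline mix. The article does not show that school will be ignored in the analysis or that schools will be changed.

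**What to change.** 1. Restate the sample size or power with a design effect over a stated ICC range (for example 0.01 to 0.05), separately for adults and children. If school was recorded on returned surveys, the T1 data could supply an estimate.
2. Say whether 444 is per park or the total at each time point, and give the category proportions behind it.
3. Where feasible, re-approach the same 18 pre-schools and schools at T3.
4. Account for school as a cluster in the park-by-wave model, by a random effect or by cluster-robust errors with a small-sample correction. Do not give postal respondents individual fixed effects: in a repeated cross-sectional survey that would remove them from the T1–T3 contrast.

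Cost: items 1, 2 and 4 are wording and model specification. The price is a less favourable stated power, particularly for children, and slightly wider intervals. Item 3 needs the schools to consent again. Correcting the statement needs no extra participants, but if the ICC proves to be above about 0.03, T3 child returns at the baseline level would not reach the restated target. The plan should then either accept that power or seek more child responses.
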